### Intervention

The intervention, 28 h in total, extends over an 8-weeks period and includes: (i) individual learning and practice (1^st^–2^nd^ wk): a one-time 1-h introduction and ice-breaking exercise at the start of the first session to be followed by a 1-h training session on self-administered acupressure provided by certified trainers in the participant’s home twice a week for 2 consecutive weeks (total, 5 h); (ii) home follow-up (3^rd^–4^th^ wk): a 1-h home visit by certified trainers to reinforce learning and self-practice once a week for 2 consecutive weeks (total, 2 h); and (iii) self-practice (3^rd^–8^th^ wk): self-administered acupressure by the participant at home, to be undertaken not less than one h after a meal, for 15 min twice a day for 6 weeks following the completion of the 2-weeks training session (total, 21 h).

For each of the 1-h training sessions during the first 2 weeks, a brief introduction to the basic theories of TCM and acupressure therapy will be provided (15 min). The introduction will be followed by a demonstration of self-administered acupressure by the trainers (15 min). Self-administered acupressure will then be practiced, until proficient, by the participant under the guidance of the trainers (30 min). The trainers, made up of a senior year TCM student and a senior year nursing student, will be trained and certified by a licensed TCM practitioner from the researchers’ School of Chinese Medicine.

For monitoring of compliance, during the 5^th^ through 8^th^ weeks of the intervention, once a week, phone calls will be made by the same team of trainers to remind the participant to perform the self-administered acupressure with feedback for any questions or expressed concerns. Any medical incidents (e.g., visits to hospital or doctor for caregiver health problems) will be documented. Each participant will use an “acupressure” diary to record the frequency, duration, and time of the acupressure conducted each day, and the record will be checked by the trainer during the telephone calls.

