### Instruments

The following study instruments (with the exception of the Demographic Questionnaire) will be administered at four time points: (a) pre-intervention (T0, baseline), i.e., on entry to study after randomization but before intervention; (b) post-training (T1, end of 2^nd^ week), i.e., on completion of the 2-weeks individual learning and practice; (c) post-intervention (T2, end of 8^th^ wk), i.e., on completion of the 8-weeks self-administered acupressure intervention; and (d) follow-up (T3, end of 12^th^ wk), i.e., 4 weeks after the completion of the intervention.The Chinese version of the Caregiver Burden Inventory (C-CBI, 24 items) [27] will be used to (i) initially screen potential participants for caregiver stress, and (ii) assess levels of caregiver stress at different time points in the study. The C-CBI has been validated for the Chinese population and demonstrated satisfactory internal consistency (Cronbach’s alpha 0.9) [27]. Each item is assessed using a 5-point Likert scale ranging from 0 (never) to 4 (nearly always). For the initial screening, participants with a summed score of ≥ 25 will be identified as experiencing caregiver stress and recruited into the study.The Chinese version of the Piper Fatigue Scale (C-PFS, 22 items) will be used to (i) initially screen potential participants for the symptom of fatigue, and (ii) assess the levels of fatigue experienced by the participant at different time points in the study. The C-PFS has been validated with good reliability (Cronbach’s alpha 0.93) [28]. Each item is assessed using a numeric scale of “0” to 10” with higher scores representing more fatigue. For the initial screening, participants with a mean score of ≥ 4 will be identified as experiencing fatigue and recruited into the study.The Chinese version of the Pittsburgh Sleep Quality Index (C-PSQI, 19 items) will be used to (i) initially screen potential participants for the symptom of insomnia, and (ii) assess the levels of insomnia experienced by the participant at different time points of the study. The C-PSQI has been validated with good reliability (Cronbach’s alpha 0.86) [29]. Insomnia (sleep disturbances in subjective sleep quality, sleep latency, sleep duration, habitual sleep efficiency, sleep disturbances, use of sleeping medication, and daytime dysfunction) will be assessed on a 4-point Likert scale ranging from 0 (no difficulty) to 3 (severe difficulty). For the initial screening, participants with a global (summed) score of > 5 will be classified as experiencing insomnia and recruited into the study.The Chinese version of the Patient Health Questionnaire (C-PHQ, nine items) will be used to (i) initially screen potential participants for the symptom of depression, and (ii) assess the levels of depression experienced by the participant at different time points of the study. The C-PHQ is one of the most popular self-administered screening tools for the symptom of depression that has been validated in the Hong Kong Chinese population [30]. Each item is scored from 0 (not at all) to 3 (nearly every day), with a total score ranging from 0 to 27. Cutoff values of 5, 10, 15, and 20 have been widely used to define mild, moderate, moderately severe, and severe depressive symptoms. For the initial screening, participants with a total score of ≥ 10 will be identified as experiencing the symptom of depression and recruited into the study.The Chinese version of the SF-12 version 2 Health Survey (C-SF-12v2, 12 items) has demonstrated validity and equivalence for Chinese populations [31] and will be used to assess health-related quality of life. The 12 items are grouped under the mental component summary and physical component summary. The survey is scored by recoding the items, computing the raw scale scores, and transforming the scores to a range from 0 to 100 according to the standard scoring algorithm. Higher scores indicate a better health status.Health economics assessment (HEA) will be assessed to determine the cost minimization [32] related to the intervention, with items on: (i) number of physician visits, (ii) use of prescription drugs, and (iii) incidence of inpatient hospitalization.A demographic questionnaire (DQ) will be used to collect information on age, education level, marital status, number and age of children, employment status, financial hardship, number of care recipients, total number of hours of caregiving per week (for the older adult care recipient and children, if appropriate), length of caring (years/months of caregiving), assistance received from other family members (including number of people providing care), paid/occasional caregivers, receipt of comprehensive social security assistance, need for financial support, and number of years living in Hong Kong. Information will also be collected regarding the care recipient’s health and dependency including age, health problems, disabilities, and degree of dependency on the caregiver.

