
### Procedures

Upon study entry, participants in both groups will be asked to complete the Chinese version of the questionnaires (T0, baseline assessment), including C-CBI for caregiver stress, C-PFS for fatigue, C-PSQI for insomnia, C-PHQ for depression, C-SF-12v2 for quality of life, HEA for cost minimization, and DQ for participant profile. The participants assigned to the intervention group will then receive the intervention as described. When the intervention group reaches post-training, post-intervention, and follow-up time points (T1, T2, and T3, respectively), participants in both groups will complete C-CBI, C-PFS, C-PSQI, C-PHQ, C-SF-12v2, and HEA. After the completion of data collection at T3, participants in the wait-list control group will then receive the self-administered acupressure training. The immediate treatment received by the intervention group, the wait-list control condition received by the control group, and the data collection points are shown in Fig. 1.

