## Discussion

This study protocol describes the implementation and evaluation of a self-administered acupressure intervention for Chinese family caregivers with caregiver stress. This will be the first randomized controlled trial to test the effectiveness of self-administered acupressure in reducing the stress of caregivers and improving their stress-related symptoms of fatigue, insomnia, depression, and health-related quality of life.

The emotional and physical strain of caregiving and its adverse impact on family caregivers’ health and well-being is recognized as a serious public health problem [3, 33, 34]. Although a variety of pharmacological and psychosocial interventions have been developed to alleviate caregiver stress, the therapeutic benefits are modest [35–37]. Therefore, there is a need to find interventions that are not only effective but also acceptable to caregivers. Providing interventions to these caregivers is challenging; not only may their motivation be hampered by the stress of never-ending caregiving responsibilities, but their needs often have to take second place after those of their care recipients. If proven effective, the self-administered acupressure intervention would open up an attainable avenue for family caregivers to release their caregiving stress in a safe, feasible, and affordable manner. By reducing the burden of caregiver stress, it is intended that the self-administered acupressure intervention will not only alleviate health declines, but also lower health and social care costs for these caregivers and their care recipients. Furthermore, the realization of what they can achieve in promoting health and well-being through self-administered intervention may also empower the caregivers to make optimal lifestyle choices.

This study has the potential of informing health and social care providers about the design and implementation of interventions to buffer the adverse effects of caregiver stress. In addition, the trial findings will also provide the much-needed evidence to apprise policy-makers of the need for socioeconomic policies to more effectively empower family caregivers to take care of themselves and their care recipients.

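### The one dedicated medical-incident record appears tied to the acupressure arm's week 5–8 calls, so a statement that the intervention is safe would be only weakly supported

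*Protocol article*

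**What the plan says.** The protocol article, under Intervention, describes compliance monitoring in the acupressure arm: "during the 5^th^ through 8^th^ weeks of the intervention, once a week, phone calls will be made by the same team of trainers". Their purpose is "to remind the participant to perform the self-administered acupressure with feedback for any questions or expressed concerns". The next sentence reads: "Any medical incidents (e.g., visits to hospital or doctor for caregiver health problems) will be documented". The one after it turns to the acupressure diary, which the trainer checks on the same calls. The incident sentence itself states no arm, no recorder and no time window.

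Events of a similar kind are also collected elsewhere. Under Instruments, the HEA has these items: "i) number of physician visits, (ii) use of prescription drugs, and (iii) incidence of inpatient hospitalization". Its stated purpose is that it "will be assessed to determine the cost minimization [32] related to the intervention". It is completed at baseline (T0), and at T1, T2 and T3, under Procedures, "participants in both groups will complete C-CBI, C-PFS, C-PSQI, C-PHQ, C-SF-12v2, and HEA". Data analysis plans a between-group comparison of the HEA by a linear mixed effects model. Randomization and blinding describes coded questionnaires and blinded data collectors. Under Procedures, the wait-list arm is trained only after T3.

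Safety is not among the aims, hypotheses or outcomes. The Discussion nevertheless expects that, if it proves effective, the intervention would "open up an attainable avenue for family caregivers to release their caregiving stress in a safe, feasible, and affordable manner".

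**The concern.** A list of incidents is informative about an intervention when the same questions are put to both randomized arms over the same period. The participants are stressed caregivers with fatigue, poor sleep or depressive symptoms, so doctor visits and minor complaints will occur without acupressure. A list kept in one arm cannot separate these from effects of the procedure. A list that opens in week 5 also passes over the period when participants first learn the technique and first practise alone. The recorders are the trainers who deliver the intervention and encourage its continuation, and they know the allocation.

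What is at stake is the description that would accompany a positive result. The Discussion's wording is triggered by effectiveness alone, and a reader could take it as resting on this trial's data. The primary comparison of caregiver stress is not affected.

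**Working it through.** The point rests mainly on reading the sections together. The only arithmetic is the coverage of the call window.

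**1. Which arm, who and when.** The incident sentence stands between two sentences about the trainers' calls, in a paragraph on compliance, under the Intervention heading. The calls remind people to practise. Wait-list participants have nothing to practise until after T3 (end of week 12). The natural reading is therefore acupressure arm, weeks 5–8, trainers. This is an inference from position, because the sentence does not say so.

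**2. Coverage on that reading.** Inputs from the Intervention section: training in weeks 1–2, home visits in weeks 3–4, self-practice in weeks 3–8 for 15 min twice a day, calls in weeks 5–8. From Instruments: T3 at the end of week 12.

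- Scheduled self-practice sessions: 6 weeks × 7 days × 2 = 84. Check against the article's own total: 84 × 15 min = 1,260 min = 21 h, which agrees with the stated 21 h.
- Sessions before the calls begin (weeks 3–4): 2 × 7 × 2 = 28, and 28/84 = 33%.
- Intervention weeks covered: 4/8 = 50%.
- Self-practice weeks covered: 4/6 = 67%.
- Weeks to T3 covered: 4/12 = 33%.
- Weeks not covered: 1–2 (training), 3–4 (home visits and first self-practice) and 9–12 (follow-up).

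**3. What the HEA adds.**

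| | Incident sentence (natural reading) | HEA |
|---|---|---|
| Arms | Acupressure | Both |
| Timing | Calls in weeks 5–8 | T0, T1, T2, T3 (baseline; ends of weeks 2, 8, 12) |
| Recorder | Trainers, who know the allocation | Participant, on coded forms; collectors stated as blinded |
| Content | Medical incidents, with doctor or hospital visits as examples | Physician visits, prescription drugs, admissions |
| Reason for visit | Not stated | Not among the listed items |
| Discomfort without a visit | Not among the examples | Not among the listed items |
| Purpose | Stands in the compliance paragraph | Cost |

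The HEA therefore supplies a concurrent randomized comparison of healthcare use. Neither source, as described, supplies a two-arm record of complaints that lead to no visit, drug or admission. Table 1 includes firm massage at several points and tapping of the low back with the fists, so any minor discomfort from these could go unrecorded.

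**4. Against the Discussion.** The safety wording would draw on a one-arm incident list over part of the exposure, a two-arm count of healthcare use without reasons, and the earlier work cited in the Background.

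**The case against.** The strongest reply has four parts.

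First, the sentence is passive and assigns no arm, period or recorder, so incidents might also be noted at the training sessions and home visits in weeks 1–4. This stands as far as it goes: the article does not exclude it. But the sentence's placement points one way, and no other occasion for recording incidents is described.

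Second, the HEA records the events that the sentence gives as examples, in both arms and under stated blinding, with a between-group analysis. A randomized comparison of visits and admissions needs no attribution of cause. This stands in full. A reader might infer that harms are collected in one arm only, or that there is no concurrent comparison at all. The documents do not support that inference. A coverage share computed over both arms from the calls alone would mislead for the same reason, since it gives the HEA no credit.

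Third, safety is not an objective, the Discussion's phrase is conditional, and the Background cites reviews and an earlier study in women with knee pain as evidence of safety. This also stands. It is why the conclusion is weak support, and not that the trial fails an aim.

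Fourth, detailed adverse-event procedures may sit in a full protocol that is not shown. That would excuse silence. Here the article states a rule and places it in one arm's compliance calls, so the placement can be criticized.

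Two further inferences should be resisted. A reader might suppose that the calls sharpen the acupressure arm's recall and bias the HEA at T2. The article does not say that participants are asked about visits each week, and it gives no HEA recall period, so this is speculation. A reader might also cite the upper confidence limit after zero events in 100 participants. That limit follows from the number of participants and would be the same under the fix, so it shows no defect.

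**Conclusion.** The concern holds in a limited form. On its natural reading, the one dedicated incident record has no match in the wait-list arm, is kept by trainers who know the allocation, and covers 4 of 8 intervention weeks, missing the first 28 of 84 scheduled self-practice sessions. The HEA partly makes up for this with a two-arm comparison of healthcare use. As listed, it lacks the reason for a visit and any discomfort that led to none. A statement from this trial that the intervention is safe would be only weakly supported.

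This rests on two assumptions: that the incident sentence belongs to the calls beside it, and that the HEA form contains no more than its listed items. If either is wrong, the gap is smaller and the article needs only to say so. The primary analysis is unaffected. This is a cheap improvement to make before data collection.

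**What to change.** Add the same short, self-completed incident items to the coded questionnaires of both arms at T1, T2 and T3: any health problem or discomfort since the last assessment, and the reason for any doctor or hospital visit. Place them after the outcome scales, so that an answer mentioning acupressure cannot reveal allocation before those scales are completed. Report the counts by arm with confidence intervals.

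State in the Intervention section which arm, period and recorder the existing incident sentence covers. The trainers' call log can continue, but it should stay out of between-arm comparisons. In the Discussion, limit the safety wording to what these data and the cited earlier work show.

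The cost is slightly longer forms at three assessments that both arms already complete, one descriptive table, a small risk that free-text answers reveal allocation, and a more cautious safety statement. No new visits or staff are needed.

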### Instruments

The following study instruments (with the exception of the Demographic Questionnaire) will be administered at four time points: (a) pre-intervention (T0, baseline), i.e., on entry to study after randomization but before intervention; (b) post-training (T1, end of 2^nd^ week), i.e., on completion of the 2-weeks individual learning and practice; (c) post-intervention (T2, end of 8^th^ wk), i.e., on completion of the 8-weeks self-administered acupressure intervention; and (d) follow-up (T3, end of 12^th^ wk), i.e., 4 weeks after the completion of the intervention.The Chinese version of the Caregiver Burden Inventory (C-CBI, 24 items) [27] will be used to (i) initially screen potential participants for caregiver stress, and (ii) assess levels of caregiver stress at different time points in the study. The C-CBI has been validated for the Chinese population and demonstrated satisfactory internal consistency (Cronbach’s alpha 0.9) [27]. Each item is assessed using a 5-point Likert scale ranging from 0 (never) to 4 (nearly always). For the initial screening, participants with a summed score of ≥ 25 will be identified as experiencing caregiver stress and recruited into the study.The Chinese version of the Piper Fatigue Scale (C-PFS, 22 items) will be used to (i) initially screen potential participants for the symptom of fatigue, and (ii) assess the levels of fatigue experienced by the participant at different time points in the study. The C-PFS has been validated with good reliability (Cronbach’s alpha 0.93) [28]. Each item is assessed using a numeric scale of “0” to 10” with higher scores representing more fatigue. For the initial screening, participants with a mean score of ≥ 4 will be identified as experiencing fatigue and recruited into the study.The Chinese version of the Pittsburgh Sleep Quality Index (C-PSQI, 19 items) will be used to (i) initially screen potential participants for the symptom of insomnia, and (ii) assess the levels of insomnia experienced by the participant at different time points of the study. The C-PSQI has been validated with good reliability (Cronbach’s alpha 0.86) [29]. Insomnia (sleep disturbances in subjective sleep quality, sleep latency, sleep duration, habitual sleep efficiency, sleep disturbances, use of sleeping medication, and daytime dysfunction) will be assessed on a 4-point Likert scale ranging from 0 (no difficulty) to 3 (severe difficulty). For the initial screening, participants with a global (summed) score of > 5 will be classified as experiencing insomnia and recruited into the study.The Chinese version of the Patient Health Questionnaire (C-PHQ, nine items) will be used to (i) initially screen potential participants for the symptom of depression, and (ii) assess the levels of depression experienced by the participant at different time points of the study. The C-PHQ is one of the most popular self-administered screening tools for the symptom of depression that has been validated in the Hong Kong Chinese population [30]. Each item is scored from 0 (not at all) to 3 (nearly every day), with a total score ranging from 0 to 27. Cutoff values of 5, 10, 15, and 20 have been widely used to define mild, moderate, moderately severe, and severe depressive symptoms. For the initial screening, participants with a total score of ≥ 10 will be identified as experiencing the symptom of depression and recruited into the study.The Chinese version of the SF-12 version 2 Health Survey (C-SF-12v2, 12 items) has demonstrated validity and equivalence for Chinese populations [31] and will be used to assess health-related quality of life. The 12 items are grouped under the mental component summary and physical component summary. The survey is scored by recoding the items, computing the raw scale scores, and transforming the scores to a range from 0 to 100 according to the standard scoring algorithm. Higher scores indicate a better health status.Health economics assessment (HEA) will be assessed to determine the cost minimization [32] related to the intervention, with items on: (i) number of physician visits, (ii) use of prescription drugs, and (iii) incidence of inpatient hospitalization.A demographic questionnaire (DQ) will be used to collect information on age, education level, marital status, number and age of children, employment status, financial hardship, number of care recipients, total number of hours of caregiving per week (for the older adult care recipient and children, if appropriate), length of caring (years/months of caregiving), assistance received from other family members (including number of people providing care), paid/occasional caregivers, receipt of comprehensive social security assistance, need for financial support, and number of years living in Hong Kong. Information will also be collected regarding the care recipient’s health and dependency including age, health problems, disabilities, and degree of dependency on the caregiver.

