### Randomization and blinding

Eligible participants will be randomly assigned to either the intervention group (*n* = 100) or the wait-list control group (*n* = 100) using a computerized blocked randomization scheme operated by the study programmer (SP) who is not involved in the recruitment. A series of random numbers will be generated to determine the group assignment of the participants. The group assignment results will be kept in separate, sealed, opaque envelopes. The entire randomization process will be securely conducted by the SP and the group assignment of participants will be centrally controlled. Neither the research assistant conducting the recruitment, nor the participant will know the group assignment until the envelope is opened.

Questionnaires will be completed by each of the participants and numerically coded to ensure that the group allocation of the participant is not revealed. The numerical codes and the names of the participants will be stored separately and securely in the central office. Researchers conducting data collection and analysis will be blinded to the group allocation of the participants.

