### Data analysis

The primary outcome is caregiver stress and the secondary outcomes are symptoms of fatigue, insomnia, depression, and health-related quality of life.

The effectiveness of the self-administered acupressure intervention on caregiver stress, symptoms of fatigue, insomnia and depression, and health-related quality of life will be assessed. To do this, the scores of the C-CBI, C-PFS, C-PSQI, C-PHQ-9, SF-12v2, and HEA collected at four different time points will be analyzed for changes from baseline (T0) to the post-intervention (T2) and from the post-intervention (T2) to the follow-up (T3).

For the primary analysis, the levels of caregiver stress on completion of the intervention (T2) between the intervention and wait-list control groups will be assessed by a regression analysis with adjustment of baseline values and accounting for any possible effect of the demographics. Residuals will be checked to ensure adequacy of the method. In addition, changes in caregiver stress from baseline (T0) to follow-up (T3) will be assessed by paired *t*-tests. The intention-to-treat principle will be adopted and all study subjects will be included in the analysis with missing values replaced by the last observed values or imputed by regression substitution.

For secondary analysis, the scores of the C-PFS, C-PSQI, C-PHQ, C-SF-12v2, and HEA will be compared for differences between the intervention and wait-list control groups by a linear mixed effects model with the baseline value of the scale and the intervention group as fixed factors and the intercept as a random factor. Moreover, effects of the demographics, care recipients’ health problems/disability, and dependency on the outcomes will be explored by considering them as fixed factors in the linear mixed effects model. Changes in mean scores from baseline will also be assessed by a linear mixed effects model with the use of linear contrasts. Multivariate analysis will also be conducted to simultaneously study changes in clusters of mean scores.

Baseline characteristics (T0) between the intervention and wait-list control groups will be assessed by chi-square test and Mann–Whitney U test for categorical and continuous data, respectively.

Statistical significance is defined as *p* < 0.05 with a two-sided test. All statistical analyses will be conducted with Statistical Package for the Social Sciences (SPSS) program.

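### T0 is scheduled after randomization and nothing keeps the arm concealed until it is complete, so the self-reported baseline used for adjustment may be affected by allocation

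*Protocol article*

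**What the plan says.** The Instruments section defines T0 as taken "on entry to study after randomization but before intervention". The Procedures section agrees that the groups already exist at that point: "Upon study entry, participants in both groups will be asked to complete the Chinese version of the questionnaires". The intervention arm starts treatment afterwards.

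On concealment, the Randomization and blinding section says: "Neither the research assistant conducting the recruitment, nor the participant will know the group assignment until the envelope is opened". It does not say when the envelope is opened relative to T0. The same section states "Questionnaires will be completed by each of the participants and numerically coded", and limits blinding to research staff: "Researchers conducting data collection and analysis will be blinded to the group allocation of the participants".

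In the Data analysis section, the primary comparison of caregiver stress at T2 is a "regression analysis with adjustment of baseline values", also accounting for demographics. The secondary mixed models carry the baseline value of each scale as a fixed factor. Changes are analysed from T0 to T2, from T2 to T3 and, for caregiver stress, from T0 to T3 by paired t-tests. Missing values may be replaced by the last observed value or by regression substitution.

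The Participants and Instruments sections also show that C-CBI, C-PFS, C-PSQI and C-PHQ are administered at screening to establish eligibility.

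**The concern.** Baseline adjustment is safe because a baseline measured before allocation cannot depend on the arm. That guarantee is lost if participants report T0 after learning their assignment. In this trial, allocation tells a stressed caregiver whether help begins at once or only after T3, at week 12. Disappointment, relief or a wish to demonstrate need could each alter answers on subjective scales, and could do so differently in the two arms. Blinding the data collectors does not prevent this, because the participant is the source of the score.

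A T0 shifted by allocation is a post-randomization variable. Adjusting for it, or subtracting it, carries the shift into the treatment estimate. Two further routes follow from the text. The demographic questionnaire is completed at T0 and includes items open to perception, such as financial hardship and the care recipient's dependency. And for someone who drops out early, carrying the last value forward could turn an affected T0 score into the T2 outcome.

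**Working it through.** **Inputs.** From the Sample size section: CBI SD 17.61, pre-post correlation 0.7, target difference 6 points, 83 per group before attrition, type I error 5%. From the Data analysis section: two-sided testing. The differential shift in T0, written δ, is not in the documents; 1 to 3 C-CBI points is an assumed range.

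**The plan's own figure.** SD of change = 17.61 × √(2 × (1 − 0.7)) = 13.64. For a 6-point difference and 80% power, the normal approximation gives 82 per group and the t-test solution is 82.1, rounded up to 83. Power at 83 is 80.9% (normal) or 80.4% (t). With 15% attrition, 83 / 0.85 = 97.6, so 98. The stated figures reproduce.

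**Effect of a shift in T0 only.** The adjusted estimate is (difference in T2 means) − b × (difference in T0 means), where b = correlation × SD(T2)/SD(T0) = 0.7 with equal SDs. A shift δ in reported T0 that has gone by T2 moves the adjusted estimate by 0.7 × δ. A between-arm comparison of changes from T0 moves by δ.

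**Operating characteristics**, normal approximation, 83 per group. The residual SD of the adjusted model is 17.61 × √(1 − 0.7²) = 12.58, so the SE is 12.58 × √(2/83) = 1.95. The change analysis uses SD 13.64. Without a shift, power of the adjusted model is 86.7%.

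| Assumed δ | Adjusted bias (share of 6) | Bias in change from T0 (share of 6) | Type I error, adjusted / change | Adjusted power if the shift runs against the intervention |
|---|---|---|---|---|
| 1 | 0.7 (12%) | 1 (17%) | 6.5% / 7.6% | 77.5% |
| 2 | 1.4 (23%) | 2 (33%) | 11.1% / 15.7% | 65.4% |
| 3 | 2.1 (35%) | 3 (50%) | 18.9% / 29.4% | 51.5% |

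**Checks.** A simulation of 4,000 trials with no true effect and the intervention arm's T0 raised by 2 points gave a mean adjusted estimate of −1.43 and a rejection rate of 11.0%, in line with the formula. With the correlation varied from 0.5 to 0.8 at δ = 2, the adjusted bias runs from 0.5 × 2 = 1.0 to 0.8 × 2 = 1.6 points.

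**Direction.** If the intervention arm reports the higher T0, the estimate moves in favour of the intervention. If the wait-list arm does, it moves against. The documents do not indicate which.

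**The case against.** The best answer is that the protocol separates generating an assignment from disclosing it. The study programmer prepares sealed, opaque envelopes, so T0 could follow randomization while the envelope is still closed. Fig. 1 was not available for this review and may show the order, and the article condenses a fuller document. This stands to the extent that a reader might infer that the envelope is opened before T0; no section says so. It does not remove the point, because the stated rule places T0 after randomization and nothing requires concealment to last until T0 is complete.

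The size rests on an assumed shift and on that shift being gone by T2. If a fraction λ of it persists to T2, the adjusted bias becomes (λ − 0.7) × δ: zero at λ = 0.7 and of opposite sign above it. The T2 score is in any case self-reported by participants who know their arm, and moving T0 does not cure that. Both remarks are fair. They make the net effect less predictable; they do not make the T0 schedule safe.

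Other stronger readings also fail:
- A reader might infer that every change score is affected. The T2 to T3 change does not use T0.
- A reader might infer that no later analysis could help. An unadjusted T2 comparison, or adjustment for screening scores, avoids T0.
- A reader might infer that intention-to-treat is impossible for someone who withdraws before T0. The plan provides for imputation, and a screening C-CBI exists for every randomized participant. The supportable statement is that T0 would be missing, perhaps more often in one arm.

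**Conclusion.** The point holds as an avoidable route to bias in the primary covariate, not as demonstrated contamination. It affects the primary T2 regression, the baseline term in the secondary models, the T0 to T2 and T0 to T3 changes, and any T0 value carried forward.

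Its illustrative size is 0.7 to 2.1 C-CBI points on the primary estimate, against a target of 6. That rests on four assumptions: the participant knows the arm at T0; the arms differ by 1 to 3 points in reported T0 as a result; the shift affects T0 only; and the correlation is 0.7 with equal SDs. The first three are not stated in the documents. The case for acting is that the timing is a stated rule, it bears on the primary analysis, and it is easily changed.

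**What to change.** In the Instruments section, redefine T0 as completed after consent and confirmed eligibility but before randomization, and include the demographic questionnaire. If randomization must come first, state in the Randomization and blinding section that the envelope is opened only after all T0 questionnaires have been completed. Align the Procedures section and Fig. 1. If the envelope is already held back in practice, one sentence saying so settles the matter. Either form removes the T0 shift due to knowledge of allocation.

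For participants already enrolled whose T0 followed disclosure, add a sensitivity analysis that replaces T0 with the pre-randomization screening scores for C-CBI, C-PFS, C-PSQI and C-PHQ. Screening C-CBI is truncated at 25 or more, so some regression to the mean is to be expected, but equally in both arms. The documents describe no screening value for SF-12v2 or the health economics assessment, so this fallback does not cover them.

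The cost is a change in the order of steps. The documents do not say whether screening, assignment and T0 share one contact; if they are separate, some scheduling effort may be needed. The sample size stays at 83 per group, 98 with attrition, rounded to 100.
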